#### Physical activity intervention

Daily physical activity is discussed at every session. Children are asked if they remember the activity recommendations and how they can achieve it. Discussions are individualized per family using the FITT principle: frequency of activity, intensity, time and type [99]. Children are instructed to rate the intensity of their activities using a modified Borg Scale [92], which shows a child climbing stairs. Children rate their intensity by identifying the picture of the child on the stairs, with at the bottom (1) representing low intensity to the top with heavily sweating, red in the face and needing to stop (10) representing high intensity. At every session, children are encouraged to attain a 6–8 scale-rating (feeling sweaty, heart beating fast) for a total of 60-min of activity per day [9]. Using this scale not only allows researchers to understand child’s perceived intensity of activity, but also links to child’s self-efficacy. Different from the standard intervention, the modified intervention focuses on weight-bearing activities, such as jumping, running, or light strength training activities. These activities are recommended by the Canadian Society of Exercise Physiology and Health Canada and are monitored at every session [9].

#### Sedentary behaviour intervention

Time spent engaging in screen time is discussed during each intervention. Parents and children are taught that screen-time should be less than 2-h per day [100]; this includes computer gaming, telephone or internet time not related to schooling and television. Children are provided with a series of activities at each intervention session that will help them decrease their screen-time behaviours. They are asked to bring the completed activities to the next session for discussion. Specifically, session 1 asks children to record their total TV time for one-week using a calendar divided by 30-minute slots. At the end of each day, if they successfully watch less than 2-h per day, they are asked to color in a star. Session 2 children are encouraged to play a BINGO activity where they choose a different activity to play each day using a similar BINGO template. The time spent performing each activity is set by the child. Session 3 includes all family members as they try to complete a 1-month walking calendar where children color in feet (1 foot = 30 min of activity). All family members are encouraged to participate in this activity. Session 4 asks children to play a game based on a walk from their house to a castle, for every 30-min of moderate-intensity activity they may progress in the game by coloring in footstep towards the castle. Sessions 5 and 6 are open to provide children the activity they preferred the most and wish to complete, such as the walking calendar or BINGO. Should the child watch less than 2-hours of screen time prior to the intervention, sedentary activity is still discussed, monitored and positively reinforced.

#### Overcoming barriers: relapse prevention

Each visit includes a discussion with the dietitian about “tricky situations”; situations where one would either not follow CFG or have time to engage in PA. These situations may place children in a vulnerable situation where they know they will not be necessarily practicing healthy lifestyle choices, suggesting they may resort back to old habits of unhealthy lifestyles. Examples of tricky situations include birthdays, holidays, other celebrations, “sleep-over” parties, rainy days and vacations. With the help of the interventionist, realistic strategies and solutions are discussed to help child and family handle the situation to ensure they stay on track either on the day of or after the event.

#### Goal setting

Goal setting is a valid tool with this age group [91] and is a successful component of treatment programs. Goal setting with children provides insight to the child’s attitude and level of understanding of discussions during the intervention. Using a template adapted from Health Canada (Website: http://www.hc-sc.gc.ca/fn-an/food-guide-aliment/educ-comm/toolkit-trousse/plan-3a-eng.php), three SMART goals are set by the child. The goals must consist of at least one nutrition and one physical activity goal. The parents are present and can help suggest goals, but the child decides which goals they wish to pursue. The SMART goals consist of the following: *specific:* “What do I want to do?”; *measureable:* “How much and how often will I do it?” ; *attainable:* “How will I do it?”; *realistic:* “Can I do it?” and *time:* “When will I do it/ When will I start?”. The child signs the contract with the dietitian and is provided a copy for home. This is the final component of every intervention. Follow-up interventions always start with a review of goals. Children are reminded to be honest and to have open discussion as to why or why not the goals were attained in order to identify why some approaches work and barriers to others. Results from the interventions are recorded as: “yes, no or sometimes”. Creating realistic goals that are attainable and set by the participant is in line with clinical recommendations [55].

### Control

The control group visits the clinic every three months for the various assessments (Table 1). Ethically, appropriate care of the control group includes receiving the exact same number of counseling sessions at the end of the study. Specifically, after participating for one year, these families are offered the same number of counselling visits (Table 2). In terms of food group recommendations, specifically milk and alternatives, children will be instructed to follow the food guide appropriate for their age (i.e. 2–3 servings of milk and alternatives for 6–8 y olds and 3 to 4 servings of milk and alternatives for ≥ 9-y olds). Children are also encouraged to engage in 60 minutes of activity per day, including a variety of cardiovascular and strength training exercises. Frequency of these counselling sessions are determined by families.

### Sample size calculation

One-hundred and sixteen overweight/ obese children will be recruited to participate in this study. Based on similar studies [93-95], this sample size provides 80% power at a 5% significance level (two-sided) to detect a mean of change of BMI Z-score of −0.2 (SD 0.3). Estimating a 10% drop out rate, we aim to recruit 39 children for control, 39 children for StTx and 39 children for ModTx.

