### Randomization and blinding

Children are randomized by a computer-generated list using stratified block randomization of three per block to maintain balance. Two stratification factors are implemented: gender and BMI (overweight and obese). In order to maintain blinding for non-intervention related measurements, children are randomized to control, StTx or ModTx groups by the registered dietitian who conducts the interventions. Participants are informed of their group at the end of their baseline visit. All other research staff are blinded.

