## Discussion

This is the first family-based lifestyle intervention that targets prepubescent overweight and obese children with the intention to ameliorate both body composition and bone mass. The study focuses on the family as a whole, recognizing that both child and parents need to set attainable goals that focus on the child and indirectly require change at the home environment level. If effective, the tools and methods used in this study can be used in existing weight loss or child obesity treatment centers. A major strength of our study is our study design, that will determine if a program of such nature can support increases in lean mass, ameliorate impaired muscle function and increase bone density (areal and volumetric) as well as changes in adiposity (fat mass) over 1 y.

Our study is unique as it considers frameworks, such as behavioural and control beliefs of parent and self-identity of child [91]. From the child’s perspective, our study will be able to track changes in these beliefs and behaviours through research-administered questionnaires. This will help us understand the child’s intentions to change their behavior in order to sustain a lifestyle of healthy eating and regular physical activity. To date, our study is the first to develop a series of questions and track over 1-y changes in a child’s personal beliefs, self-perceptions and behaviours. Furthermore, we will be able to correlate these behavioral changes with changes in BMI Z-scores and changes in body composition from DXA. Unlike other studies, our intervention also includes a bone component, where we will be able to assess changes in dietary intake and physical activity as they relate to bone health, measured by DXA and pQCT.

The methods presented in this study build on previous work and findings in the area of child education, dietetic practice and nutritional assessments. Few studies have examined the effects of a long intervention of 1-y to reduce adiposity in children. This study is adequately powered to investigate the changes in both bone and body composition as they relate to the study group.

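### The stated 80% power holds for one unadjusted two-arm comparison, not for the planned family-wise-controlled pairwise comparisons (about 66% per pair); the recruitment total also appears as both 116 and 117

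*Protocol article*

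**What the plan says.** The section on sample size calculation opens with a total: "One-hundred and sixteen overweight/ obese children will be recruited". It then says that "this sample size provides 80% power at a 5% significance level (two-sided"), "to detect a mean of change of BMI Z-score of −0.2 (SD 0.3"), and closes with "Estimating a 10% drop out rate, we aim to recruit 39 children for control, 39 children for StTx and 39 children for ModTx". It names no test, does not say whether the −0.2 is a difference between arms, and mentions no adjustment for comparing three arms.

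The statistical analysis section compares the groups under a mixed effects ANOVA model. Significant group differences are then localized by post-hoc testing, with Tukey's method as the example, adjusted so that the family-wise error rate is 0.05. The hypothesis at the end of the Background expects a lower BMI Z-score in the modified-treatment arm than in both the standard-treatment arm and the control arm.

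**The concern.** Two things in one short paragraph do not line up with the rest of the plan.

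- **Total.** Both 116 and 3 × 39 are recruitment figures, so dropout cannot explain the difference between them.
- **Power.** The calculation is set at a two-sided 5% level with no multiplicity adjustment, but the analysis holds 5% across all comparisons of three arms. A single comparison therefore faces a higher critical value than the sample size allows for.

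The second matters more. If modified treatment did not differ significantly from standard treatment or from control, readers would judge that result against a stated 80% chance of detection. The planned test has a clearly lower chance on the same inputs.

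**Working it through.** **Inputs.** From the sample size section: difference 0.2, SD 0.3, two-sided 5%, power 80%, dropout 10%, 39 per arm. From the statistical analysis section: family-wise error rate 0.05 over three groups, Tukey as the example. Assumption: 0.2 is the between-arm difference in change, and 0.3 is the SD of change in each arm.

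**1. The total.** 39 + 39 + 39 = 117, against 116 stated: one child, or 0.9%.

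**2. Reproducing the plan's figures.** Normal formula, per arm:

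n = 2 × (1.960 + 0.842)² / (0.2/0.3)² = 35.3 (35.32 unrounded, with exact normal quantiles).

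Allowing for dropout by multiplication: 35.32 × 1.10 = 38.85, which rounds to 39 per arm. Three times the unrounded value is 116.56, which truncates to 116. Both stated sizes can thus come from one calculation rounded in two ways.

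**3. Power of one unadjusted comparison after dropout.** 39 × 0.9 = 35.1, so about 35 completers per arm.

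- Standard error of the difference: 0.3 × √(2/35) = 0.0717.
- Standardized difference: 0.2 / 0.0717 = 2.789.
- Normal approximation: Φ(2.789 − 1.960) = Φ(0.829) = 79.6%.
- Noncentral t: 78.5%.

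At 39 per arm with no dropout, the same steps give 83.7% (normal) and 82.8% (t). The stated 80% is therefore a fair description of one unadjusted comparison after dropout.

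**4. Power of one pair under Tukey, three arms.** The critical value for a pairwise t statistic is q(0.95; 3, df)/√2, with df = 3n − 3.

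| Per arm | df | Standardized difference | Tukey critical value | Power for a given pair |
|---|---|---|---|---|
| 35 (after 10% dropout) | 102 | 2.789 | 2.378 | 65.9% |
| 39 (no dropout) | 114 | 2.944 | 2.375 | 71.5% |

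A quick check on the first row: Φ(2.789 − 2.378) = Φ(0.411) = 65.9%. A Bonferroni adjustment for three comparisons at 35 per arm gives 65.4% (normal) or 63.2% (t), so the result does not hang on the choice of Tukey.

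The gap from 80% is about 14 points at 35 per arm. Even with no dropout, 39 per arm does not reach 80%.

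**The case against.** **The 80% may be meant for the overall test.** With 105 completers in total, the overall F test across three arms has 81.8% power if one arm differs from the other two by 0.2, and 69.1% if the arms are evenly spaced over 0.2. The first pattern is compatible with the hypothesis, so this reading cannot be excluded. But the section gives one mean change and no pattern of three means. Even on this reading, the 80% would not carry over to the pairwise comparisons that decide which arms differ.

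**Tukey is only an example, and the model may do better.** This stands in part. The mixed model may use covariates and repeated measurements, and either could reduce the error variance. The 66% is therefore an approximation from the stated SD, not the exact power of the final model. The family-wise rate of 0.05 is not an example, however; it is a stated requirement, and Bonferroni gives much the same answer.

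**Stronger readings that the document does not support.**

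- A reader might infer that the 80% is itself miscalculated, because the t-test gives 78.5%. The section names no test, the normal formula gives 79.6%, and a gap of 1.5 points or less is a matter of method and rounding.
- A reader might infer that 39 per arm is too few, since rounding up at each step gives 36/0.9 = 40 (normal) or 37/0.9 = 41.1, so 42 (t-test). Again this is rounding: 35.1 expected completers against 35.32 required.
- A reader might infer that 116 breaks the randomization because it is not a multiple of three. The plan uses "stratified block randomization of three per block" within strata of gender and BMI category. Incomplete blocks can arise in any stratum, so a total divisible by three is neither needed nor enough for equal arms.
- A reader might take "This study is adequately powered" in the Discussion as a repeat of the 80%. That sentence concerns bone and body composition, whereas the calculation is for BMI Z-score.

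**Conclusion.** The point holds in two parts of unequal weight. The double total, 116 and 117, is an editorial slip of one child with no bearing on design or power. The material part is that the stated 80% applies to one unadjusted two-arm comparison, while the plan controls the family-wise error rate at 0.05 over three arms. For a given pair, power is then about 66% at 35 completers per arm and about 71% at 39 per arm with no dropout.

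This rests on reading 0.2 as the between-arm difference with SD 0.3, on equal arms, on Tukey as the adjustment, and on no gain from covariates or repeated measures.

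**What to change.** In the sample size section:

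- Give one recruitment target, 117 (39 per arm), and say that about 35 completers per arm are expected after 10% dropout.
- Say that the 0.2 is a between-arm difference, if that is what is meant, and that the 80% refers to one unadjusted pairwise comparison at two-sided 5%.
- Add that under the planned Tukey adjustment, power for a given pair is about 66%, before any gain from covariates or repeated measures.

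This takes a sentence or two. Enrolment and analysis stay as they are. The downside is that the stated power looks less favourable.

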## Discussion

This is the first family-based lifestyle intervention that targets prepubescent overweight and obese children with the intention to ameliorate both body composition and bone mass. The study focuses on the family as a whole, recognizing that both child and parents need to set attainable goals that focus on the child and indirectly require change at the home environment level. If effective, the tools and methods used in this study can be used in existing weight loss or child obesity treatment centers. A major strength of our study is our study design, that will determine if a program of such nature can support increases in lean mass, ameliorate impaired muscle function and increase bone density (areal and volumetric) as well as changes in adiposity (fat mass) over 1 y.

Our study is unique as it considers frameworks, such as behavioural and control beliefs of parent and self-identity of child [91]. From the child’s perspective, our study will be able to track changes in these beliefs and behaviours through research-administered questionnaires. This will help us understand the child’s intentions to change their behavior in order to sustain a lifestyle of healthy eating and regular physical activity. To date, our study is the first to develop a series of questions and track over 1-y changes in a child’s personal beliefs, self-perceptions and behaviours. Furthermore, we will be able to correlate these behavioral changes with changes in BMI Z-scores and changes in body composition from DXA. Unlike other studies, our intervention also includes a bone component, where we will be able to assess changes in dietary intake and physical activity as they relate to bone health, measured by DXA and pQCT.

The methods presented in this study build on previous work and findings in the area of child education, dietetic practice and nutritional assessments. Few studies have examined the effects of a long intervention of 1-y to reduce adiposity in children. This study is adequately powered to investigate the changes in both bone and body composition as they relate to the study group.

Nevertheless, counselling obese children poses unique challenges and barriers, including lack of overall family involvement, identifying participant motivation, support services, time and reimbursement [102]. Although including all family members in all sessions is important, it is true for some it may not benefit the child, particularly if parental level of support or willingness to change behaviour is not beneficial to the child [103]. A strength of the MY LIFE Study is the focus on the family environment and allows for sessions to be tailored to family needs. Our study offers continuous support to families by having dietitians available at all visits and conducting all follow-up visits at times that meet family needs. It is important that clinicians are capable of identifying behaviors that contribute to the child’s weight status and are able to work with the child to modify these behaviors [104]. The MY LIFE Study interventions are designed in a manner to support these needs, by using standard documentation techniques that utilize study tools (CEB-Q and PAQ-C) and still allow for variability of counselling topics. The MY LIFE Study provides an excellent example of how national educational tools, specifically the Canada’s Food Guide and Physical Activity Guide, can be used in a clinical setting. We believe that employing a family-centered approach that considers the family environment, developmental stage, as well as food and activity preferences will improve the program’s success. A focus on fun yet feasible activities will assist both children and parents in adhering to the program.

The results of the MY LIFE Study will be published in 2014 in relevant organizations and peer-reviewed academic journals. The study protocol presented in this paper is anticipated to help others who research the same area, and ultimately in creating treatment programs to combat childhood obesity.

## Abbreviations

PA: Physical activity; StTx: Standard treatment; ModTx: Modified treatment; CFG: Canada’s food guide; TTM: Transtheoretical model; BMI: Body mass index; BMD: Bone mineral density; DXA: Dual-energy x-ray absorptiometry; pQCT: Peripheral quantitative computed tomography; vBMD: Volumetric bone mineral density; aBMD: Area bone mineral density; MYLIFE: McGill youth lifestyle intervention for food and exercise; BMC: Bone mineral content; CIQ: Child intention questionnaire; FHQ: Family health questionnaire; PAQ-C: Physical activity questionnaire for children; CHQ: Child health questionnaire; CEB-Q: Child eating behavior questionnaire.
